### Outcome measures

The following outcomes and variables will be collected during this trial;

Primary outcome: live birth, defined as the birth of a living child beyond 24 weeks of gestational age.Pregnancy course monitoring: ultrasound biometric outcomes, gestational age at time of pregnancy loss (if applicable).Pregnancy complications, such as hypertensive disorders and gestational diabetes.Delivery and postpartum details, including delivery method and postpartum complications.Neonatal information: weight, percentile, presence of congenital abnormalities, gestational age and other relevant factors.

Additionally, digital questionnaires will be administered to patients at various intervals during the follow-up period. These include:

Hospital Anxiety Depression scale and EQ-5D-5L at randomization, 3, 6, and 12 months post-randomization to assess maternal quality of life.iMedical Consumption Questionnaire at 6 and 12 months post-randomization to evaluate maternal medical expenses.iProductivity Cost Questionnaire (iPCQ) at 6 and 12 months to measure maternal productivity loss.Medication diary: common side effects of prednisolone (nausea and vomiting, mood swings, hypertension, hyperglycaemia and weight gain) will be monitored using digital medication diaries to evaluate compliance and adverse reactions.

#### Monitoring and safety

The study is a Consortium study supported by the Dutch Consortium for Healthcare Evaluation and Research in Obstetrics and Gynaecology (NVOG). It receives support and assistance from the Trial Office (Zorgevaluatie Nederland) and has established a Data and Safety Monitoring Board (DSMB) in recognition of the study’s moderate risk level.

This independent DSMB will perform ongoing safety surveillance, a planned safety evaluation (after 100 randomisations) and monitoring of serious adverse events (SAEs). The DSMB’s recommendations will be communicated solely to the study sponsor.

Prednisolone, a corticosteroid with anti-inflammatory and immunosuppressant qualities, is a commonly administered drug. Much experience has been gained with this drug, also in pregnancy, for treating rheumatoid arthritis, asthma or bowel disease.^40^ In addition, some women are given this medication during pregnancy as part of a transplantation regimen. Thus, side effects are well established and known. In pregnancy, prednisolone is metabolised in the placenta to the inactive prednisone. Only 10% of active compound reaches the fetus.^41^ When the use is chronic and in high dosages (>10 mg daily), it is possibly associated with fetal growth restriction and in the third trimester with neonatal adrenal cortical insufficiency.^42^ Based on available studies and two registries, there is substantial evidence showing that prednisolone in the dosage used in the study (20 mg) and usage in the first trimester is safe for mother and fetus. Animal studies showed an association with cleft palate when high dosages of dexamethasone were used; earlier studies have not shown an increased risk for congenital abnormalities with prednisolone in humans.^43 44^ The most common side effects comprise mood changes, weight gain, indigestion, hypertension and hyperglycaemia. In an earlier feasibility trial, none of the side effects were severe enough for women to stop taking medication, and no suspected unexpected serious adverse reactions (SUSAR) or adverse fetal outcomes were reported.^35^

### Sample size calculations

For this superiority trial, we based the sample size on an absolute treatment effect of 12%; in between the by patients and healthcare practitioners predefined, minimally important difference of 10% and a maximal expected difference of 18%. The latter number is based on the treatment effect observed in the meta-analysis by Dan *et al*.^45^ The validity of this meta-analysis is, however, questionable,^46^ and the effect was shown only in a subpopulation of patients with high uNK cell density. We therefore decided on a more conservative approach and calculated the sample size based on a treatment effect of 12%. To demonstrate this increase in the LBR (χ^2^ test, power 80%, two-sided α 0.05) from 63% in the control group (as observed in an earlier large trial in Dutch population^26^) to 75% in the prednisolone group, we need to include 464 patients. Assuming a 5% loss to follow-up, the total number of participants required is 490, with 245 in each arm.

### Statistical analysis

#### Data analysis

We engaged the expertise of statisticians and methodologists to ensure meticulous planning of the data analysis. Additionally, a health technology assessment (HTA) expert was employed to contribute to the cost-effectiveness analysis (CEA) of the research.

The analysis of the gathered data will involve several methodological approaches:

Demographic information about the studied population will be presented using descriptive statistics, depicted in tables.

The primary outcome is live birth. We will first report the observed number (and percentage) of live births in the treatment and placebo groups. Following the recommendations of the The United States Food and Drug Administration (FDA) for covariate adjustment in clinical trials,^47^ to increase power, we compared the LBRs between the intervention and control group using a multivariable logistic regression analysis, taking into account strong predictors of pregnancy loss, in this case, maternal age and previous number of pregnancy losses.^3^ From this multivariable model, we will derive an estimate of the marginal treatment effect, expressed as an absolute risk difference, along with 95% CI, using standardisation and bootstrapping. The statistical significance threshold will be set at p<0.05, and all analyses will be performed using SPSS or R.

Secondary outcomes and subgroup analysis

Next to the primary outcome, we will consider the following secondary outcomes

Pregnancy loss, defined as the spontaneous demise before the 24th week of gestation.Ongoing pregnancy, defined as viability of the fetus beyond the 12th week of gestation.Tolerability (defined as percentage of non-compliance due to side-effects).Safety of prednisolone (including congenital abnormalities, gestational weight, SAEs and SUSARs).Side-effects to the mother or the fetus and the cost-effectiveness of the treatment.

Again, following the recommendations of the FDA for covariate adjustment in clinical trials,^47^ to increase power, we compared the secondary outcomes between the intervention and control group using a multivariable logistic regression analysis, taking into account strong predictors of pregnancy loss (maternal age and previous number of pregnancy losses).^3^ From this multivariable model, we will derive an estimate of the marginal treatment effect, expressed as an absolute risk difference, along with 95% CI, using standardisation and bootstrapping. The statistical significance threshold will be set at p<0.05.

In addition, we will perform subgroup analyses to explore the effect of prednisolone in the following participant categories:

Women with positive thyroid peroxidase antibodies.Women with positive antinuclear antibodies.Women with high and low levels of prepregnancy endometrial uNK cells, macrophages and regulatory T cells*.*Participants age (≤36 or >36 years old).Number of previous pregnancy losses (≤3 or >3).

We will employ appropriate statistical tests to assess secondary outcomes such as safety parameters, side-effects and quality of life measurements. Depending on the nature of the data (continuous or categorical), t-tests, χ^2^ tests or regression analyses will be applied.

A detailed statistical analysis plan, developed with the expertise of the employed statisticians, will be published prior to the closure of the database on www.zorgevaluatienederland.nl/premi (publicly available).

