### Participants and eligibility criteria

Eligible patients are women aged 18–39 years with ‘unexplained recurrent pregnancy loss’, defined as the loss of two or more pregnancies, without a known cause for RPL (such as antiphospholipid syndrome, congenital uterine abnormalities or abnormal parental karyotype). As fetal aneuploidy is the most common cause of pregnancy loss, but more often not tested in case of pregnancy loss, women with potentially aneuploid losses are eligible to participate. The diagnosis of unexplained is based on the latest ESHRE guideline (including biochemical pregnancy losses).^3^ Patients who meet any of the following criteria will be excluded from participation in this study:

Instable, or exacerbation of, auto-immune diseases such as thyroid disease or inflammatory bowel disease.Diabetes mellitus requiring medical treatment.Current treatment with systemic corticosteroids (for any indication) or other immunosuppressive medication.Simultaneous enrollment in any other trial that studies the effectiveness of an intervention in RPL or previous enrolment in the PREMI trial.Contraindications to prednisolone use.Use of drugs with known interaction with prednisolone.

Patients can enroll in the study either during early pregnancy (<7 weeks gestation), with randomization performed at enrollment, or before conception if they ave an active desire to conceive, with randomization delayed until pregnancy is confirmed. Both women who conceive spontaneously and those who conceive through artificial reproductive techniques are eligible for participation.

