### Procedures, recruitment and randomisation

The total (planned) enrolment period of the study is 30 months, with a subsequent 12 month follow-up. Eligible patients will be identified by local research coordinators and/or staff members trained in ‘good clinical practice’ at participating hospitals. Patients will receive verbal, written and/or video-animated information. When signing the informed consent form, non-pregnant patients will be requested to collect and send in menstrual blood from the first 24 hours of menstruation to the coordinating centre (Leiden University Medical Centre, LUMC) for the isolation of endometrial immune cells. Upon confirmation of pregnancy (urine or blood test) <7 weeks gestational age, randomisation takes place, in a 1:1 ratio, using Castor EDC with variable randomisation blocks (4, 6 and 8). Patients will be assigned to the intervention or placebo group, with allocation blinded to investigators, participants, clinicians and research coordinators.

Data will be collected in a web-based registration system, Castor (CDMS 2023.4). Once a patient is randomised, the research nurse will collect data in the electronic case report form provided in Castor. Database cleaning will be conducted by internal consistency checks and identification of database entries outside expected ranges. Patients will receive standard care with their own treating physician or midwife. All collected data will be coded, processed and stored with adequate precautions to ensure patient confidentiality. This is described in a separate data management plan.

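### The adjusted models leave out gestational age at randomisation, a pre-treatment value needed for eligibility; adding it would give a small, cheap gain in precision

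*Protocol article*

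**What the plan says.** In the protocol article, the Data analysis section compares live birth between arms by multivariable logistic regression, "taking into account strong predictors of pregnancy loss, in this case, maternal age and previous number of pregnancy losses". The stated purpose of adjusting is to gain power. The model is then standardised to a marginal absolute risk difference with a bootstrap confidence interval. The part on secondary outcomes repeats the same two covariates and the same method.

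Two sections bear on gestational age. Under Participants and eligibility criteria: "Patients can enroll in the study either during early pregnancy (<7 weeks gestation), with randomization performed at enrollment, or before conception", the second route having randomisation deferred until pregnancy is confirmed. Under Procedures, recruitment and randomisation: "Upon confirmation of pregnancy (urine or blood test) <7 weeks gestational age, randomisation takes place, in a 1:1 ratio". That section gives variable block sizes and names no stratification factor.

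The maternal items under Baseline information are previous losses, age, parity, BMI and medical conditions. Gestational age at randomisation is not named there.

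**The concern.** If the aim of adjustment is power, the natural test of the covariate set is whether it leaves out a baseline variable that is available, precedes treatment and carries prognostic information. Gestational age at randomisation appears to meet all three conditions.

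- **Available.** Eligibility cannot be applied without it.
- **Pre-treatment.** It is fixed before allocation.
- **Prognostic, in direction at least.** If S(t) is the probability of no recognised loss by gestational age t, then for otherwise similar women P(live birth | no loss by t) = P(live birth) / S(t). This cannot fall as t rises.

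No stated design feature balances it between arms. At stake is a little precision in the primary risk difference, plus protection against a chance imbalance that a reader of the baseline table might later ask about.

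**Working it through.** **1. The plan's own figure.** Inputs from Sample size calculations: "χ^2^ test, power 80%, two-sided α 0.05"; live birth "from 63% in the control group" "to 75% in the prednisolone group, we need to include 464 patients".

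n per arm = [z(0.975)·√(2·p̄·q̄) + z(0.80)·√(p₁q₁ + p₂q₂)]² / d², with p̄ = 0.69 and d = 0.12.

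- 1.960 × √0.4278 = 1.282
- 0.842 × √(0.2331 + 0.1875) = 0.546
- (1.282 + 0.546)² / 0.0144 ≈ 232 per arm, or 464 in total
- 464 / 0.95 = 488.4, so 489, or 490 for equal arms

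Both stated figures reproduce. They rest on an unadjusted test with 80.0% power at 464, so no stated number depends on the covariate set.

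**2. What gestational age would add.** The documents give neither its effect on live birth nor its distribution, so everything here is assumed: gestational age uniform over 4 to 7 weeks; standardised maternal age and number of losses with log odds ratios of −0.4 and −0.3; N = 464; 63% v 75%; 4,000 simulated trials per row. Each trial was fitted with and without gestational age and standardised to a risk difference. The SE is the spread of those estimates. Power is from the Wald test of the treatment coefficient.

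| Assumed OR per week | Control live birth at 4, 5, 6, 7 weeks | SE without → with | Power without → with |
|---|---|---|---|
| 1.2 | 57, 61, 65, 69% | 0.0421 → 0.0421 | 81.7 → 82.1% |
| 1.5 | 49, 59, 68, 75% | 0.0415 → 0.0412 | 80.7 → 81.8% |
| 2.0 | 40, 56, 71, 83% | 0.0408 → 0.0393 | 81.7 → 84.2% |
| 2.5 | 33, 54, 74, 87% | 0.0411 → 0.0389 | 82.4 → 86.6% |

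The SE falls by about 0, 1, 4 and 5%. The Monte Carlo error of a single power figure is √(0.81 × 0.19 / 4000) ≈ 0.6 points, so the first row is essentially no gain. For scale, the two planned covariates together added 1.4 to 1.9 points over no adjustment in the same runs.

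**3. A second set of assumptions.** Half the women enter at 4 to 5.3 weeks and half at 5 to 7 weeks (1,500 trials per scenario).

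| Control live birth, 4 weeks to near 7 weeks | Variance ratio, with / without | Power without → with |
|---|---|---|
| 55% to 73% | 0.984 | 80.9 → 82.2% |
| 50% to 79% | 0.970 | 80.3 → 81.7% |
| 44% to 84% | 0.959 | 82.3 → 83.3% |

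The gain is 1.0 to 1.4 points.

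**4. Validity without the covariate.** In the runs of step 2, the model with age and losses alone gave a mean estimate of 0.119 to 0.120 against a true 0.12. Its type I error was 4.9 to 5.5%. Omission does no harm to either.

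**5. Chance imbalance.** The SD of a uniform over 3 weeks is 3/√12 = 0.866. The SE of the difference in means is 0.866 × √(2/232) = 0.080, so a 2-SE imbalance is about 0.16 weeks. The gradients in step 3 are 18/3 = 6, 29/3 = 9.7 and 40/3 = 13.3 points per week. Such an imbalance would move the unadjusted difference by about 1.0, 1.6 and 2.1 points, against a design effect of 12. The confidence interval already allows for this variation; adjustment would remove it.

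**The case against.** The strongest reply is that nothing here is wrong. A valid adjusted analysis need not contain every prognostic variable, two sensible covariates are prespecified, and the sample size does not rely on adjustment at all. A detailed analysis plan is promised before database closure and could add a covariate. All of this stands. It limits the point to a suggestion, but the article does name its covariates outright, so a suggestion to extend them is in order.

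A reader might also infer three stronger things, none of which the documents support.

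- **That gestational age strongly predicts live birth.** The article calls only maternal age and previous losses strong predictors and gives no gradient for gestational age. The direction can be argued; the strength is assumed. Randomisation needs only a urine or blood test, so some women randomised later may carry a loss not yet recognised, which would flatten the gradient.
- **That it differs by entry route.** This is plausible, because women enrolled before conception may be randomised soon after a positive test. But no distribution is given, and women enrolled in pregnancy may also enter very early.
- **That its omission biases the result.** Step 4 of the working shows otherwise. Chance imbalance is possible for any unadjusted variable and is covered by the interval and the alpha level.

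One practical objection also holds: eligibility strictly needs only a judgement that gestation is below 7 weeks. The article does not show that an exact value is stored, and error in dating would shrink the gain.

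**Conclusion.** The point holds as a low-priority improvement. The models for the primary and secondary outcomes omit a pre-treatment variable that must be ascertained for every woman and plausibly carries prognostic information, although the stated aim of adjusting is power. The cost of omission is small: under assumed odds ratios of 1.2 to 2.5 per week, roughly 0 to 5% in the standard error and 0.4 to 4 points of power, with about 1 point at moderate gradients. Gains above 2 points appear only at assumed odds ratios of 2.0 or more per week, which imply control live birth running from 40% or less at 4 weeks to 83% or more at 7 weeks.

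The figures rest on assumed gradients and entry distributions. Validity, type I error and the stated 464 and 490 are untouched.

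**What to change.** - Name gestational age at randomisation among the baseline variables and confirm that it is stored as a value (in days), with the dating method stated.
- In the statistical analysis plan, before unblinding, prespecify it as a continuous covariate alongside maternal age and number of previous losses in the logistic models for live birth, pregnancy loss and ongoing pregnancy. Then standardise to the marginal risk difference as already planned.

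The cost is one extra parameter, negligible at this sample size, and one field that the eligibility check already calls for. Timing matters: the same covariate added after unblinding could be read as selective adjustment.

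### The rule for quality-of-life scores permits unadjusted t-tests for HADS and EQ-5D-5L although a baseline score is collected, which would make intervals wider than needed

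*Protocol article*

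**What the plan says.** Under Outcome measures, the protocol article schedules "Hospital Anxiety Depression scale and EQ-5D-5L at randomization, 3, 6, and 12 months post-randomization to assess maternal quality of life". Each responding woman therefore has a baseline score and up to three follow-up scores on each scale.

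Under Statistical analysis, in the part on secondary outcomes and subgroups, two paragraphs bear on how secondary outcomes are compared.

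- The first adopts covariate adjustment in order to raise power. It uses a multivariable logistic model, "taking into account strong predictors of pregnancy loss (maternal age and previous number of pregnancy losses"), and reports a marginal absolute risk difference. The baseline questionnaire score is not among the covariates.
- The second covers safety, side-effects and quality of life: "We will employ appropriate statistical tests to assess secondary outcomes such as safety parameters, side-effects and quality of life measurements". Its selection rule is "Depending on the nature of the data (continuous or categorical), t-tests, χ^2^ tests or regression analyses will be applied".

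The section then defers detail: "A detailed statistical analysis plan, developed with the expertise of the employed statisticians, will be published prior to the closure of the database".

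**The concern.** The stated criterion for choosing the quality-of-life method is the type of data. For a continuous score in two arms, that criterion is fully met by a plain two-sample t-test at each visit. It takes no account of what matters most for these outcomes, namely that the same score was recorded at randomisation. No baseline term is named in either paragraph.

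This sits awkwardly with the article's own reasoning. It adjusts the binary outcomes for maternal age and number of losses to gain power. The logistic model and the risk difference do not fit HADS or EQ-5D-5L scores unless these are dichotomised, so the continuous scores fall to the data-type rule. There, the covariate likely to be most closely related to the follow-up score may go unused.

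At stake is precision. An unadjusted comparison leaves chance baseline differences between the arms in the estimate and gives wider intervals than the collected data allow. The wording also leaves open a choice between a t-test and regression that is better settled before the data are seen.

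**Working it through.** **1. The plan's own figure.** The only sample size stated is for live birth. Inputs from Sample size calculations: "χ^2^ test, power 80%, two-sided α 0.05", "from 63% in the control group", "to 75% in the prednisolone group, we need to include 464 patients". With the pooled-variance formula and no continuity correction:

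n per arm = [1.960 × √(2 × 0.69 × 0.31) + 0.842 × √(0.63 × 0.37 + 0.75 × 0.25)]² / 0.12² = 232, so 464 in total, an exact match. Allowing for 5% loss, 464 / 0.95 = 488.4, so 489, or 490 with equal arms of 245. The plan's figure is reproduced. No precision or sample size is stated for HADS or EQ-5D-5L.

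**2. Inputs for the questionnaire scores.**

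- Women per arm: 232 (the evaluable number above), taken as if all of them answer.
- Standard deviation: not given, so results are in SD units.
- Correlation r between baseline and follow-up score: not given. Assumed, and shown over 0.3 to 0.7.

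**3. Unadjusted t-test at one visit.** The 95% half-width is 1.96 × √(2/n) = 1.96 × √(2/232) = 0.182 SD. With 245 per arm it is 0.177 SD.

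**4. Adding the baseline score at the same visit (ANCOVA).** The variance is multiplied by 1 − r², so the half-width is 0.182 × √(1 − r²). The penalty for leaving the baseline out is a width factor of 1/√(1 − r²), and the equivalent sample-size factor is 1/(1 − r²).

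| r (assumed) | ANCOVA half-width (SD) | t-test interval relative to ANCOVA | Equivalent sample size |
|---|---|---|---|
| 0.3 | 0.174 | 1.05 | 1.10 |
| 0.4 | 0.167 | 1.09 | 1.19 |
| 0.5 | 0.158 | 1.15 | 1.33 |
| 0.6 | 0.146 | 1.25 | 1.56 |
| 0.7 | 0.130 | 1.40 | 1.96 |

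The ratios in the last two columns do not depend on the number of women, so lower questionnaire response changes the half-widths but not the relative loss.

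**5. What the figures do and do not support.** They are single-visit results. They show the value of adjusting for the baseline score, and do not by themselves favour a mixed model over ANCOVA at each visit. Averaging the three visits would narrow the interval further, but that is a different, time-averaged estimand and is not counted here.

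**The case against.** The strongest objection is that the article states nothing wrong. Regression stands beside the t-test in the list, so a baseline-adjusted analysis is already allowed, and the choice of covariates and the handling of visits are matters an article commonly leaves to the SAP. Much of this stands, and it rules out several stronger readings.

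- **That the plan commits to t-tests and ignores baseline.** A reader might infer this from the data-type rule. The text does not assign these scores to t-tests, does not say visit by visit, and does not exclude the baseline score.
- **That HADS is a key tolerability result, because mood change is a known effect of prednisolone.** The article defines tolerability as non-compliance due to side-effects, assigns mood swings to the medication diary, and gives HADS and EQ-5D-5L the purpose of assessing quality of life. The treatment course lasts 8 weeks, so if it starts promptly after randomisation it ends before the 3-month questionnaire.
- **That t-tests would be biased by dropout after pregnancy loss and a mixed model would cure this.** The documents give no questionnaire response rates and no link between response and loss. A mixed model helps only so far as the observed scores explain the missingness, and a woman with no follow-up score is absent from either analysis.

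What the objection does not remove is that the article goes beyond silence. It publishes a selection rule, and that rule admits a less efficient method when a better one needs only data already collected.

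**Conclusion.** The point holds as a matter of efficiency. As worded, the rule permits unadjusted t-tests for HADS anxiety, HADS depression and EQ-5D-5L. If that option were taken, single-visit 95% intervals would be about 5% wider than needed at a correlation of 0.3, 15% at 0.5 and 40% at 0.7. The correlation is an assumption, and at the low end of the range the loss is small.

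The consequence is confined to the precision of these questionnaire outcomes. With complete data the unadjusted randomised comparison remains unbiased, and the primary analysis of live birth is not affected. The SAP may already settle the matter; it is not shown. This is an improvement available at almost no cost, not an error that endangers the trial's conclusions.

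**What to change.** In the SAP, replace the t-test option for the continuous HADS anxiety, HADS depression and EQ-5D-5L scores with a baseline-adjusted analysis. Either of these would do, provided one is named in advance:

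- ANCOVA at each of 3, 6 and 12 months, with treatment and the baseline score of the same scale; or
- one linear mixed model over 3, 6 and 12 months, with treatment, visit, treatment-by-visit, baseline score, baseline-by-visit, maternal age and number of previous losses.

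Report adjusted mean differences with 95% confidence intervals at each visit. ANCOVA already recovers the whole gain calculated above. The mixed model also brings the three visits into one analysis, but should not be presented as resolving non-response related to pregnancy loss.

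The cost is a few sentences of SAP wording and standard code. No new data are needed, and the article places publication of the SAP before database closure, so the change fits the stated timetable.
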